## Method

### Study design and setting

This will be a multicentre, assessor-masked (‘blind’), individual, parallel-arm RCT (trial registration: NCT05223959). Participants will be recruited from psychiatric units of teaching and non-teaching hospitals in seven centres: Karachi (target *n* = 150), Lahore (target *n* = 50), Multan, Rawalpindi, Peshawar, Hyderabad and Quetta (target *n* = 20 at each). By recruiting participants from across the country, we are confident that the sample will be representative of Pakistani patients with bipolar disorder.

### Participants

Participants meeting the eligibility criteria (Appendix 1) will be included in the study.

### The CaPE intervention

CaPE is a manualised intervention for bipolar disorder consisting of 12 one-to-one psychoeducation sessions, one session per week. The decision to deliver the intervention individually is based on our pilot study^24^ and takes into account local cultural norms and expectations regarding the delivery of mental healthcare. From our experience in large trials of psychosocial interventions in Pakistan, participants are uncomfortable sharing experiences of mental illness in group settings because of local beliefs and the stigma associated with mental illness. Each CaPE session (Appendix 2) lasts for approximately 1 h, beginning with a 20–30 min presentation on the topic of the session, followed by a related exercise (e.g. drawing a life chart or compiling a list of potential triggers for recurrence). The manual is a modified and culturally adapted version of the Barcelona Bipolar Disorders Program.^25^ Master's-level clinical psychologists will facilitate all sessions. Pakistan produces over 3000 Master's-level psychologists each year, and these clinicians are an underused resource, making it feasible and economically sustainable for them to deliver CaPE individually. The same psychologist will deliver all 12 sessions to ensure continuity. Psychologists will receive regular weekly supervision from local co-investigators to maintain fidelity.

#### Cultural adaptation of psychoeducation

Our group has culturally adapted interventions for depression, postnatal depression, self-harm and psychosis using mixed methods, in Pakistan and the UK. The framework used considers three areas: assessment and engagement, awareness of cultural factors and adjustments in implementation.^26,27^ Most cultural adaptations of psychological treatments tend to be for implementation rather than content,^28^ and we use the same principle for the CaPE intervention. We use culturally acceptable idioms when explaining the concept, causes and symptoms of bipolar disorder (sessions 1–3), taking into account participants’ lay perceptions of the causes and treatment of mental illness. We also use local folk stories and images (e.g. to explain the concept of multiple perspectives) as well as examples from religious teachings. To improve engagement, we incorporate simple strategies that have worked in the past. These include speaking in the native language (Urdu), using culturally appropriate terms instead of jargon, and establishing a good rapport and a trusting relationship during the sessions. If the participant agrees, we also involve the main carer and family in sessions, particularly sessions 6, 7 and 8 (risks of treatment discontinuation and detection and management of relapse).

### Control condition (TAU)

Local medical, psychiatric and family medicine services provide routine care according to their clinical judgement and available resources. Treatment as usual (TAU) will be ascertained by the participant's treating physician. Research staff will record the nature and intensity of TAU delivered to each participant. In current practice, people with bipolar disorder are not routinely referred for any psychological therapies in Pakistan. TAU for the disorder in Pakistan largely comprises pharmacotherapy.

### Outcome measures

The primary outcome measure is time (in weeks) to recurrence of a mood (depressive/manic/hypomanic/mixed) episode. This will be assessed at each follow-up using the Longitudinal Interval Follow-up Evaluation (LIFE),^29^ an integrated system for assessing the longitudinal course of psychiatric disorders. The assessment will consist of a semi-structured interview, during which an interviewer uses the LIFE to collect detailed psychosocial, psychopathological and treatment information for the follow-up interval. The weekly psychopathology measures are ordinal symptom-based scales with categories defined to match the criteria of DSM-5. Additional secondary measures are listed in Appendix 3.

All scales (both self-report and clinician-rated) will be administered using a tablet, to allow results to be safely and instantly loaded to the study database, with paper versions available if there are technological difficulties. All scales will be translated into Urdu and back-translated into the original language. Most have been used in previous studies in Pakistan, including our pilot.^24^

### Study procedures

We have seven major recruitment centres, each with multiple out-patient psychiatric units. There are five recruitment sites in Karachi, three in Lahore and one each in Multan, Rawalpindi, Peshawar, Hyderabad and Quetta. Psychiatrists will identify potential participants and offer them information about the study. Those who agree will be contacted by the research team, pre-screened and provided detailed information about the study, including procedures protecting privacy and confidentiality. Potential participants will have a chance to ask questions prior to providing informed written consent. Participants will then undergo a screening assessment based on the eligibility criteria outlined in Appendix 1, followed by the baseline assessment. After that, an independent statistician will check the record of baseline measures and will randomise the participant to one of the two arms of the study. The participant will be contacted by the study coordinator at their recruitment centre within 1 week of randomisation to inform them about treatment allocation. The time and date of sessions will be set based on the participant's preference. Participants randomised to the intervention arm will be offered 12 weekly individual sessions. Each session will last for 60 min. All sessions will be delivered by a trained therapist, who will receive 2 months of training from senior therapists before starting the intervention. Assessments will be carried out at baseline and at 3, 6 and 12 months. The assessment scales will be administered in person and/or via secure videoconferencing software (an alternative to in-person assessment to allow for COVID-19 or travel restrictions) by trained research analysts masked to treatment allocation.

#### Randomisation and masking

Participants will be randomised using a block randomisation technique in a 1:1 allocation to CaPE or TAU. Randomisation will be computer generated and use a random permuted block method with variable block sizes. The sample will be stratified by site, bipolar type (I or II) and self-reported biological sex, given the potential differences in recurrence rates in these groups. In line with best practice in RCTs, we have not included further stratification variables.^38^ We will assess other potential prognostic characteristics (age, duration of illness, number of previous episodes, gender) in our *a priori* subgroup analyses.

This will be an assessor-masked RCT. Owing to the nature of the interventions, clinicians in participating centres and the participants themselves cannot be masked to treatment allocation. Before assessments, participants will be asked not to reveal any information about treatment to assessors. To avoid unmasking, outcome assessors will be located separately from treatment providers, and we will assign new outcome assessors in cases of unintentional unmasking. Statistical analysis will be partially masked (knowing treatment groups, but not what each group is). The intention-to-treat analysis plan will help reduce the effect of attrition bias. Finally, registration on Clinicaltrials.gov and publication of results regardless of the outcome will both minimise reporting bias.

### Sample size

From preliminary evidence collected during the pilot RCT,^24^ we estimated the mean time to recurrence as 10 weeks in the TAU group and 45 weeks in the CaPE group. This resulted in a hazard ratio of 4.51. For the purposes of the current study, we assumed a more conservative mean time to recurrence of 21.4 weeks for the TAU group. For a sample size of 240 (120 in each group), we would have more than sufficient power (0.91) to detect a low hazard ratio of 1.60, which approximately corresponds to a mean relapse time of approximately 34.2 weeks in the CaPE group, a difference that would be of clinical importance. The minimum detectable hazard ratio to attain 0.80 power is 1.49. To allow for a possible 20% attrition rate, we aim to recruit 300 participants in total. For within-subgroup analysis, the minimum detectable hazard ratio is 1.67 for larger groups (e.g. males, ~60% of the sample based on pilot-trial data) and 1.88 for smaller groups (e.g. females, ~40% of the sample based on pilot-trial data). For subgroups defined by medium cut-off points, the minimum detectable hazard ratio is 1.75. For the current design, we could only detect between-group differences in treatment effects with adequate power (0.80) when there are drastic group differences, for example a hazard ratio of 1.75 in one group and 3.5 in another. As the effectiveness of CaPE is not yet established, it is premature to further increase our sample size to power subgroup analyses. Nevertheless, preliminary subgroup analysis will inform power calculations for future studies.

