#### Subgroup analyses

Subgroup analysis will be carried out with respect to age, duration of illness, number of previous episodes, gender and self-reported biological sex by adding a treatment with covariate interaction into the primary analysis model.

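### The 0.80 power claimed for detecting a subgroup difference (hazard ratio 1.75 versus 3.5) is about 0.65 on the plan's own assumptions

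*Protocol article*

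**What the plan says.** The Sample size section of the protocol article rests its power figures on 240 analysed participants ("For a sample size of 240 (120 in each group"), which is the 300 recruited less 20% attrition. For the control arm, "we assumed a more conservative mean time to recurrence of 21.4 weeks for the TAU group". It then claims "more than sufficient power (0.91) to detect a low hazard ratio of 1.60", which it equates with "a mean relapse time of approximately 34.2 weeks in the CaPE group". It adds: "The minimum detectable hazard ratio to attain 0.80 power is 1.49". Within subgroups it gives minimum detectable hazard ratios of 1.67 (about 60% of the sample), 1.88 (about 40%) and 1.75 (a split at the median).

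It then turns from effects within a subgroup to differences between subgroups. The design is said to detect these only "with adequate power (0.80) when there are drastic group differences, for example a hazard ratio of 1.75 in one group and 3.5 in another". The Subgroup analyses section makes this the relevant test: five covariates (age, duration of illness, number of previous episodes, gender, biological sex) are to be examined "by adding a treatment with covariate interaction into the primary analysis model".

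**The concern.** An interaction compares two treatment effects, each estimated in only part of the sample, so its standard error is about twice that of the overall effect. The section's own figure of 1.75 is the smallest hazard ratio that half the sample can detect with 0.80 power. Contrasting two such halves multiplies the variance by about two. The detectable ratio of hazard ratios should then be near exp(√2 × ln 1.75) = 2.2, before allowing for the fewer events expected where the hazard ratio is 3.5. The plan claims 0.80 for a ratio of 3.5/1.75 = 2.0.

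This is the only figure in the section that describes the interaction test actually planned, and it errs in the favourable direction. At the stated effect the chance of missing the interaction would be about 35%, not 20%, so a null interaction would be weaker evidence than the text implies. The section also says the subgroup results will inform power calculations for later studies, which makes an accurate figure useful.

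**Working it through.** **Inputs from the protocol article**
- Analysed sample 240, 120 per arm; TAU mean 21.4 weeks (Sample size).
- Allocation "in a 1:1 allocation to CaPE or TAU" (Randomisation and masking).
- Recurrence observed within 12 months, taken as 52 weeks; two-tailed 0.05 (Statistical analysis).
- Hazard ratios are TAU over CaPE, so the CaPE mean is 21.4 × HR.

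**Assumption.** Times to recurrence are exponential. The plan does not say so, but its own conversion fits: 34.2/21.4 = 1.60.

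**Step 1: reproduce the plan's other figures.** The probability of recurrence by 52 weeks is 1 − exp(−52/mean).
- TAU: 1 − exp(−52/21.4) = 0.912.
- CaPE at HR 1.60: 1 − exp(−52/34.24) = 0.781.
- Expected events: 120 × (0.912 + 0.781) = 203.2.
- Schoenfeld power: Φ(√203.2/2 × ln 1.60 − 1.96) = 0.918.

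Solving the same formula for 0.80 power gives the detectable hazard ratios:

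| Figure | Plan | Recomputed |
|---|---|---|
| Power at HR 1.60, n = 240 | 0.91 | 0.918 |
| Detectable HR, n = 240 | 1.49 | 1.48 |
| Detectable HR, 60% (n = 144) | 1.67 | 1.66 |
| Detectable HR, 40% (n = 96) | 1.88 | 1.88 |
| Detectable HR, median split (n = 120) | 1.75 | 1.75 |

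The model therefore matches the basis of the plan's calculation closely, including its use of 240 rather than 300.

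**Step 2: the interaction, equal subgroups of 120 (60 per arm).**
- CaPE recurrence probability at HR 1.75: 1 − exp(−52/37.45) = 0.751.
- CaPE recurrence probability at HR 3.5: 1 − exp(−52/74.9) = 0.501.
- Events: d₁ = 60 × (0.912 + 0.751) = 99.8; d₂ = 60 × (0.912 + 0.501) = 84.8.
- Effect: ln(3.5/1.75) = 0.693.
- SE = √(4/99.8 + 4/84.8) = 0.2955.
- z = 0.693/0.2955 = 2.35; power = Φ(2.35 − 1.96) = **0.65**.
- With the variance taken as the sum of 1/events over the four arm-by-subgroup cells: SE = 0.303, z = 2.28, power = **0.63**.

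Two simulations of the Cox interaction test at n = 240 gave 0.64 (4,000 replicates) and 0.66.

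**Step 3: other readings of the sentence.** All keep two-sided 0.05 and 52-week censoring unless stated.

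| Variant | Power |
|---|---|
| n = 240, 60/40 split, either direction | 0.60 to 0.64 |
| n = 240, 21.4 weeks read as a median | 0.58 |
| n = 240, CaPE mean held at 34.2 weeks in both subgroups | 0.70 to 0.71 |
| n = 240, CaPE hazard higher instead of lower | 0.745 |
| n = 240, one-sided 0.05 | 0.74 to 0.76 |
| n = 240, every participant has a recurrence | 0.77 |
| n = 300, no attrition, equal subgroups | 0.72 to 0.75 |

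**Step 4: what would give 0.80.**
- At n = 240, with 1.75 in the first subgroup, the second needs about 4.04 (pooled variance) to 4.18 (four-cell variance) with equal subgroups. With a 60/40 split it needs about 4.1 to 4.3.
- Keeping 1.75 versus 3.5 with equal subgroups needs about 343 to 361 analysed participants.

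**The case against.** The case for leaving the sentence alone has three parts.

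**The example is under-specified.** The sentence gives neither the subgroup proportions nor a TAU mean for each subgroup, and it follows directly on the recruitment target of 300. With 300 participants and the CaPE mean held at 34.2 weeks in both subgroups, two-sided power is 0.80. With a TAU mean of 10 weeks, the pilot value, in both subgroups it is 0.82. This shows that the n = 300 result of 0.72 to 0.75 depends on a TAU mean of 21.4 weeks in both subgroups. It does not rescue the claim. The first route implies TAU means of 34.2/1.75 = 19.5 and 34.2/3.5 = 9.8 weeks, which do not average to 21.4. The second uses the value the plan replaced with 21.4 weeks. Both ignore the attrition allowance, while the neighbouring detectable hazard ratios are clearly based on 240. At 240, no choice of recurrence rates can help enough, because the ceiling with every participant relapsing is 0.77.

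**A two-group calculation may not describe the test.** Age, duration of illness and number of episodes could enter as continuous terms. That is true, but the sentence itself speaks of one hazard ratio in each of two groups, and it is that claim which is checked here.

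**The plan already plays the subgroup analyses down.** It calls the detectable differences drastic, declines to power for them and describes the analysis as preliminary. This stands, and it limits the harm: few careful readers would treat a null interaction as decisive. It does not make the stated power correct.

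**Conclusion.** The concern holds. On the assumptions that reproduce the section's other power figures, the power to detect 1.75 versus 3.5 is about 0.65 (0.63 to 0.65 with equal subgroups, 0.60 to 0.64 at 60/40), some 15 points or more below the stated 0.80. The result rests on exponential times, which the plan's conversion of means to hazard ratios supports, and on a TAU mean of 21.4 weeks in both subgroups. The conclusion that 0.80 is not reached with 240 analysed participants at two-sided 0.05 does not depend on the recurrence rates, since the figure with no censoring is 0.77. The primary comparison, its sample size and the subgroup method are untouched. This is a wrong figure in a secondary power statement, and it should be corrected.

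**What to change.** Change the one sentence in the Sample size section, in either of two ways:
- keep 1.75 versus 3.5 and state power of about 0.65 (equal subgroups, 240 analysed, two-sided 0.05); or
- keep 0.80 and give the example as 1.75 in one subgroup and about 4.1 in the other, on the same basis.

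If 0.80 came from different inputs, state them: the number analysed, the subgroup split and the TAU mean in each subgroup.

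It would also help to say that interactions will be reported as estimates with confidence intervals. The section already makes clear that the trial is not powered for them, so this adds little beyond emphasis. The cost is one less favourable number. Sample size, design and analysis do not change.

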### Statistical analysis

The intention-to-treat principle will be used, with participants analysed according to their allocated group. Our primary outcome is time to recurrence observed within 12 months. The treatment effect will be evaluated using the Cox proportional-hazards model with treatment assignment as the primary predictor. Baseline measures of key clinical characteristics (duration of illness, number of previous episodes) and demographics (age, gender, self-reported biological sex) will be controlled in the model. The treatment effect will be illustrated by the estimated hazard ratio to relapse between the two groups. In addition, parametric survival analysis models^38^ will be employed when appropriate. In the widely used Weibull distribution case (for example), the parametric analysis will use a log-linear model on the scale parameter with treatment assignment as the primary predictor while controlling for the set of covariates described above. The regression coefficient on treatment assignment can be interpreted as the log hazard ratio between the two treatment conditions in terms of relapse. This will help estimate the mean time to recurrence for the two groups. As this is a multicentre trial, dependencies for participants from the same centre will be accounted for by including centre as a random effect.^25^ We will investigate levels of missing data, assumptions (e.g. missing at random) and predictors of missingness. Missingness will be addressed using multiple imputations, capitalising on fitting mixed models with maximum likelihood and appropriate sensitivity analyses.^39^ We will also conduct an exploratory mediation analysis to investigate the role of treatment adherence and bipolar disorder type (I or II) on 12-month outcomes. Statistical inference will be conducted using two-tailed tests with 0.05 as the level of significance and 95% confidence intervals with secondary outcomes adjusted for multiple comparisons as necessary. We will use the most appropriate analytic and graphical features of SPSS, STATA and R as relevant.

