### Eligibility criteria

Inclusion criteria

- Adult out-patients age 18 years and above
- Diagnosis of DSM-5 bipolar disorder (both bipolar disorder I and bipolar disorder II), currently in remission, confirmed by Structured Clinical Interview for DSM-5 (SCID)
- Currently euthymic (17-item Hamilton Rating Scale for Depression score <8 and Young Mania Rating Scale score <8)
- Able to give informed consent
- On stable psychiatric medication regimen for at least 3 months
- Resident of the trial catchment area.

Exclusion criteria

- Active substance use disorder, based on DSM-5 criteria
- Currently experiencing recurrence (mania, hypomania, mixed or depressive
- Active suicidal ideation
- Unstable residential arrangements that reduce likelihood of being available for the duration of trial.

## Appendix 2

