### Assessment schedule

**Table d64e765:**

Instrument	Baseline	Month 3	Month 6	Month 12
Demographic questionnaire	✓			
SCID Longitudinal Interval Follow-up Evaluation (LIFE)^29^	✓	✓	✓	✓
Young Mania Rating Scale (YMRS)^30^	✓	✓	✓	✓
17-item Hamilton Rating Scale for Depression (HRSD-17)^31^	✓	✓	✓	✓
EuroQol-5D (EQ- 5D)^32^	✓	✓	✓	✓
Bipolar Recovery Questionnaire (BRQ)^33^	✓	✓	✓	✓
4-item Morisky Medication Adherence Scale (MMAS-4)^34^	✓	✓	✓	✓
Bipolar Knowledge and Attitudes Questionnaire (BKAQ)^33^	✓	✓	✓	✓
Client Service Receipt Inventory (CSRI)^35^	✓	✓	✓	✓
Childhood Trauma Questionnaire (CTQ)^36^	✓	✓	✓	✓
Illness Perception Questionnaire-Revised^37^	✓	✓	✓	✓

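### The primary Cox model leaves out baseline HRSD-17 and YMRS, which every participant provides; adding them costs almost nothing and gains power if they predict recurrence

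*Protocol article*

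**What the plan says.** All references are to the protocol article.

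- **Statistical analysis.** For the primary Cox model, "Baseline measures of key clinical characteristics (duration of illness, number of previous episodes) and demographics (age, gender, self-reported biological sex) will be controlled". Centre is handled by "including centre as a random effect". The parametric survival model takes the same covariates.
- **Subgroup analyses.** The interaction tests are built on the primary model, so they inherit the list.
- **Outcome measures.** The primary outcome is time in weeks to recurrence of a depressive, manic, hypomanic or mixed episode.
- **Appendix 1, Eligibility criteria.** Entry requires "Currently euthymic (17-item Hamilton Rating Scale for Depression score <8 and Young Mania Rating Scale score <8", together with remission confirmed by SCID and at least three months on a stable medication regimen.
- **Appendix 3, Assessment schedule.** The entries "17-item Hamilton Rating Scale for Depression (HRSD-17)^31" and "Young Mania Rating Scale (YMRS)^30" are both ticked at baseline and at months 3, 6 and 12.
- **Sample size.** Power is given as 0.91 for a hazard ratio of 1.60 with 240 participants and a TAU mean of 21.4 weeks. No covariate adjustment is mentioned.

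**The concern.** The list covers illness history and demographics but contains no measure of symptom level at entry. The two scales that rate the symptoms making up the outcome are on file for everyone and are not used in the primary model. Randomisation is not stratified on them either (Randomisation and masking).

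In a Cox model, leaving out a covariate that truly predicts the event lowers power for the treatment effect and moves the estimated hazard ratio closer to 1. Residual symptoms are an obvious candidate predictor of relapse. The entry limit narrows their range, but eight levels remain on each scale. At stake is efficiency: whether the trial gets all the precision available from data it collects anyway. The covariates also need to be named in advance, because adding them after results are known would look data-driven.

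**Working it through.** **1. Reproducing the planned power.** Inputs from Sample size and Statistical analysis: 120 per group, TAU mean 21.4 weeks, hazard ratio 1.60, two-sided 0.05, 12 months taken as 52 weeks. The CaPE mean is 21.4 × 1.60 = 34.24 weeks. Exponential times are assumed.

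- TAU events: 120 × (1 − exp(−52/21.4)) = 120 × 0.912 = 109.4
- CaPE events: 120 × (1 − exp(−52/34.24)) = 120 × 0.781 = 93.7
- Total: about 203
- Schoenfeld: Φ(√(203.15/4) × ln 1.60 − 1.96) = Φ(3.35 − 1.96) = 0.918
- Freedman: Φ(√203.15 × 0.60/2.60 − 1.96) = Φ(3.29 − 1.96) = 0.908

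The stated 0.91 is reproduced by formulas that contain no covariates.

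**2. What the two scores could add.** The documents give no prognostic strength, so a range is assumed. The simulation used 3,000 trials per row with 240 participants allocated 1:1, exponential times, censoring at 52 weeks and a hazard ratio of 1.60 conditional on the scores. The two scores were independent and uniform on 0 to 7, giving SD = √((8² − 1)/12) = 2.29. A Cox model was fitted with and without them.

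| Assumed prognostic HR per SD, each scale | Power with scores | Power without | Points forgone | HR without scores |
|---|---|---|---|---|
| 1.0 | 0.915 | 0.917 | 0 | 1.60 |
| 1.1 | 0.916 | 0.909 | 1 | 1.59 |
| 1.2 | 0.922 | 0.894 | 3 | 1.58 |
| 1.35 | 0.905 | 0.843 | 6 | 1.53 |
| 1.5 | 0.903 | 0.783 | 12 | 1.48 |
| 2.0 | 0.891 | 0.602 | 29 | 1.39 |

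With the scores in the model, the hazard ratio stays at about 1.60 to 1.61 throughout. The simulation error on a power near 0.90 is √(0.9 × 0.1/3000) ≈ 0.005, so the first row shows no difference. The last row is included only to show the direction. It implies a hazard 2^(14/2.29) ≈ 70 times higher at 7 and 7 than at 0 and 0, and no weight is put on it.

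**3. Sensitivity to the spread of scores.** In remitted patients, scores may pile up near zero. A second simulation (1,500 trials per cell) assumed scores skewed towards zero with SD about 1.77, and is compared here with the uniform case at the same effect per scale point. Each cell gives power without, then with, the scores.

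| Rise in hazard per point | Uniform on 0–7 | Skewed to zero |
|---|---|---|
| 10% | 0.88, 0.92 | 0.89, 0.91 |
| 15% | 0.83, 0.90 | 0.88, 0.91 |
| 20% | 0.78, 0.91 | 0.85, 0.91 |

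At 5% per point the difference is negligible in both cases. Under the uniform spread, 10%, 15% and 20% per point correspond to 1.10^2.29 = 1.24, 1.15^2.29 = 1.38 and 1.20^2.29 = 1.52 per SD, so the two tables agree. With skewed scores, the forgone power at 15% and 20% drops from 7 and 13 points to about 3 and 6.

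**The case against.** The case for leaving the list alone is substantial, and most of it stands.

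- **Prognostic strength is unknown.** Nothing in the article shows that these scores predict recurrence among people already in remission. The larger losses need strong effects: 15% and 20% per point imply a 7-fold (1.15^14) and 13-fold (1.20^14) range of hazard among patients all classed as euthymic. This stands, so the gain can only be stated conditionally.
- **The listed covariates may already carry some of the information.** The simulations left out previous episodes, duration of illness, age, sex and centre. Any correlation of these with residual symptoms would shrink the increment. This stands.
- **The planned power is not affected.** A reader might infer that the trial falls short of 0.91. The documents do not support that. The figure reproduces with no covariates, and 1.60 is the ratio of the group means (34.2/21.4), most naturally read as not conditional on symptom scores. On that reading, adjustment adds to 0.91 and restores nothing.
- **The estimate is not biased.** A reader might also infer that the unadjusted hazard ratio is wrong. The shift towards 1 is non-collapsibility: the model without the scores targets a different hazard ratio, one that does not condition on them. The test keeps its error rate, which already allows for chance imbalance.
- **The choice of covariates is a judgement.** Nothing in the sentence is misstated or contradicted. This stands as far as calling it an error goes. But the section already opts for a covariate-adjusted hazard ratio and names its covariates, so asking which variables earn a place is fair. It is also not a detail simply left to an analysis plan that is not shown.

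Bipolar type, a stratification factor, is missing from the same list. That is a separate matter and does not bear on this one.

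**Conclusion.** The point holds as a low-cost improvement and not as an error in the plan. The omission is plain, and both scores should be available for every randomised participant. The size of the gain is not known from the documents. It rests on assumed prognostic strength, an assumed spread of scores, exponential times, no correlation with the listed covariates, and 1.60 read as conditional on the scores. Under the uniform spread, the forgone power runs from nil to about 3 points up to 1.2 per SD, and from about 6 to 12 points at 1.35 to 1.5. It is less if scores cluster near zero.

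The case for acting is the asymmetry. If the scores carry no information, including them costs essentially nothing (0.915 against 0.917). If they do, the trial gains power from data it already holds.

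**What to change.** Add baseline HRSD-17 and YMRS totals, as continuous terms, to the pre-specified covariates of the primary Cox model. Use the same set in the parametric survival model and in the subgroup interaction models, so that all three condition on the same variables. State that the reported hazard ratio is conditional on this set. Make the change before any outcome data are seen by treatment group.

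The cost is one sentence in the analysis section and two degrees of freedom against about 203 expected events. It needs no new data, no change in sample size and no change to the stated power.

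### The primary Cox model covers two of the three randomisation strata and leaves out bipolar type, which may forgo a modest amount of power

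*Protocol article*

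**What the plan says.** All places are in the protocol article.

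- *Randomisation and masking*: the sample is to be "stratified by site, bipolar type (I or II) and self-reported biological sex, given the potential differences in recurrence rates in these groups".
- *Statistical analysis*, adjustment in the primary Cox model: "key clinical characteristics (duration of illness, number of previous episodes) and demographics (age, gender, self-reported biological sex) will be controlled in the model". This list is not introduced as an example.
- The same section adds that "dependencies for participants from the same centre will be accounted for by including centre as a random effect". The parametric survival model (Weibull is the example given) uses the same covariates.
- Bipolar type appears once in that section, in an "exploratory mediation analysis to investigate the role of treatment adherence and bipolar disorder type (I or II) on 12-month outcomes".
- *Subgroup analyses*: "Subgroup analysis will be carried out with respect to age, duration of illness, number of previous episodes, gender and self-reported biological sex". Bipolar type is not among these.

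**The concern.** A factor is normally made a stratum because it is thought to be prognostic, and the article gives that reason for all three of its strata. The usual counterpart is to carry the strata into the primary model. Here sex and centre are carried over and bipolar type is not, although the covariates are listed by name. An analysis plan that follows the article will repeat the omission, and one that adds type will depart from the published primary model.

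The Cox hazard ratio is non-collapsible. Leaving out a prognostic factor moves the treatment hazard ratio towards 1 even when the factor is perfectly balanced between the arms, and the test loses some power compared with the adjusted one. At stake are efficiency and agreement between design and analysis.

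**Working it through.** **Inputs from the article.** 240 analysed (120 per arm), TAU mean 21.4 weeks, hazard ratio 1.60 (TAU against CaPE, so above 1 favours CaPE), 12 months of follow-up taken as 52 weeks, and "two-tailed tests with 0.05 as the level of significance".

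**Step 1: reproduce the plan's power.** With exponential times, expected events per arm are 120 × (1 − exp(−52/mean)).

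- TAU: 120 × (1 − exp(−52/21.4)) = 109.4.
- CaPE: mean 21.4 × 1.60 = 34.24 weeks, so 120 × (1 − exp(−52/34.24)) = 93.7.
- Total: 203.

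Power by Schoenfeld = Φ(√203 × ln 1.60 / 2 − 1.96) = 0.918. By Freedman = Φ(√203 × 0.60/2.60 − 1.96) = 0.908. The article states 0.91. For the minimum detectable hazard ratio of 1.49 there are 206 events, giving 0.816 and 0.806 against the stated 0.80. The planning figures reproduce, and neither formula contains a covariate.

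**Step 2: the effect of omitting type.** The article gives neither the split between types I and II nor the effect of type on recurrence. Both are varied as assumptions. Each setting has 2,500 simulated trials with n = 240, type balanced across arms, censoring at 52 weeks, and a treatment hazard ratio of 1.60 within type. Paired entries are for 20% / 50% of the sample in the higher-risk type.

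| Assumed type HR | Estimated HR, type omitted | Estimated HR, type included | Power, omitted | Power, included | Difference (points) |
|---|---|---|---|---|---|
| 1.0 | 1.609 / 1.600 | 1.612 / 1.602 | 0.924 / 0.908 | 0.923 / 0.909 | −0.1 / 0.1 |
| 1.25 | 1.596 / 1.594 | 1.602 / 1.602 | 0.916 / 0.906 | 0.919 / 0.908 | 0.3 / 0.2 |
| 1.5 | 1.589 / 1.583 | 1.602 / 1.605 | 0.904 / 0.900 | 0.912 / 0.916 | 0.8 / 1.6 |
| 2.0 | 1.559 / 1.548 | 1.592 / 1.607 | 0.886 / 0.886 | 0.910 / 0.918 | 2.4 / 3.2 |
| 3.0 | 1.534 / 1.479 | 1.604 / 1.605 | 0.854 / 0.814 | 0.912 / 0.905 | 5.8 / 9.1 |

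Each power carries a simulation standard error of about √(0.9 × 0.1 / 2500) = 0.006. Both models are fitted to the same simulated trials.

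**Step 3: where there is no spare power.** At the plan's minimum detectable hazard ratio of 1.49, with an assumed 30% in the higher-risk type and 4,000 trials per setting, power with type against without it is 0.81 against 0.79 (type HR 1.5), 0.82 against 0.78 (2.0) and 0.82 against 0.75 (2.5).

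**Step 4: validity.** With no treatment effect and type omitted, the rejection rate is 0.029 to 0.056 across the settings. The lowest values come with the strongest type effects. The test is valid to conservative.

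**Limits.** The simulations leave out the other covariates and the centre effect. If duration of illness or number of previous episodes shares prognostic information with type, the gain from adding type would be smaller.

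**The case against.** The strongest objection concerns what 1.60 means. The *Sample size* section ties it to mean times for the whole arms (21.4 and about 34.2 weeks), so it can be read as a marginal hazard ratio. On that reading the planned power belongs to the model without type. A simulation with 30% in one type, 2,000 trials per setting, and the within-type hazard ratio raised until the marginal one is about 1.60 gives power without type of 0.92 at type hazard ratios of both 2.0 and 2.5, and power with type of 0.94 and 0.96. The omission then costs none of the planned 0.91 and forgoes about 2 to 4 points on top of it. This stands. It changes what is called lost, but it still favours including type.

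It is also fair that the article speaks only of potential differences in recurrence. A reader might infer that the rates are known to differ by type, which the article does not say. At an assumed type hazard ratio of 1.25 the gain is negligible.

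Two further inferences are tempting and are not supported:

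- **Gender alongside sex.** A reader might infer that entering gender and biological sex together also costs power or dilutes the treatment hazard ratio. A check with a 60/40 sex split, an assumed sex hazard ratio of 1.3, and 2, 5 or 10 of 240 people discordant gave a treatment standard error of 0.1395–0.1396 with sex alone and 0.1398–0.1400 with both. Power moved by no more than 0.3 points. Only the standard error of the sex coefficient grew, from 0.14 to 0.36–0.90. The article treats the two as distinct variables, and its planned gender interaction needs the gender main effect, so there is no case here for removing gender.
- **Site against centre.** A reader might infer a mismatch because "five recruitment sites in Karachi, three in Lahore and one each in Multan, Rawalpindi, Peshawar, Hyderabad and Quetta" makes 13 recruitment sites in seven centres. The abstract also calls the seven cities sites, so the article does not show that the two levels differ. The exact level is a detail commonly left to the analysis plan.

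**Conclusion.** The point holds as a modest matter of efficiency and consistency. One of three randomisation strata, chosen for a possible link with recurrence, is missing from a covariate list that the article fixes by name, and no other section repairs this. The planned mediation analysis is no substitute, because bipolar type is settled before randomisation and cannot lie on the path from treatment to outcome.

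If type is prognostic, leaving it out gives a hazard ratio nearer to 1 than the type-adjusted one. It forgoes about 0 to 2 points of power for a type hazard ratio up to 1.5, about 2 to 4 points at 2.0, and about 6 to 9 points at 3.0. These sizes rest on assumed prevalences of 20% to 50%, assumed type effects and exponential times. Power for a hazard ratio of 1.60 stayed above 0.80 in every setting.

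A reader might infer that the stated power of 0.91 is wrong or that the primary test is invalid. Neither follows: the figure reproduces, and type I error is not inflated.

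**What to change.** In *Statistical analysis*, add bipolar type (I/II) to the primary Cox model, either as a covariate or as a Cox stratum, and add it to the parametric model. Fix the choice before unblinding so that it remains pre-specified.

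The cost is one sentence and at most one degree of freedom against roughly 200 expected events. No new data are needed, because type is already recorded for randomisation.
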